### Recruitment of patients

Patients starting with treatment will be recruited from 30 community pharmacies in different areas of The Netherlands in the period between May 2011 and March 2013.

Patients in the intervention arm will be selected through an automated selection procedure and presented to the pharmacist. This selection is based on dispensing data and most inclusion and exclusion criteria are incorporated. The same selection will be used to include patients in the usual care group. However not all exclusion criteria can be incorporated in the automated selection and after selection, pharmacist can decide not to include a patient. We will ask the pharmacist to register the reason. However due to the study design the possibility of introducing a selection bias exists, and therefore our primary analysis will be based on the intention-to-treat principle (ITT). Patients will be included in the analysis if they are eligible according to selection criteria based on the pharmacy data. In a per-protocol (PP) analysis we will compare the patients who actually received counselling with patient who received usual care.

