### Sample size

Power calculation is focused on the primary outcome, the proportion of adherent patients. With a type one error (α) for a two sided test of 0.05 and a probability of rejecting the null hypothesis of 0.80 (1-β) 294 patients per arm are needed for demonstrating an improvement of the proportion of adherent patients from 70% to 80% [32]. For cluster randomisation a correction is needed based on the Intraclass correlation coefficient (ICC). When using ICC = 0.02 we need at least 15 pharmacies to include at least 30 patients per group of medication for the intervention (4), so 15*30*4 = 1800 patients in the intervention arms and 1800 in the usual care arms. We expect an average response rate of 30% on the questionnaires and with the aim to receive at least 100 responses per arm, we estimated to invite at least 670 patients to participate in the survey.

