### Statistical analysis

The primary analysis is based on the intention-to-treat (ITT) principle e.g. in the intervention group all patients who should have received the intervention will be included. Patient characteristics between groups will be compared using Student’s t-test or χ^2^- test. Because it is likely that the PDC360 will not be normally distributed, PDC360 differences between groups will be compared using the nonparametric Mann–Whitney U test. We use logistic multilevel analysis to study the effect on the dichotomous primary outcome (adherent yes or no). The outcome of complete discontinuation will be assessed using Cox-proportional hazards. We consider a p-value of less than 0.05 to be statistical significant. In a second analysis effect modification and confounding will be assessed. Effect modification is defined as a significant interaction (p < 0.10) between group allocation and the variable in question. In a per-protocol (PP) analysis we include in the intervention group only patients who actually received the call.

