### Limitations

The cluster randomized design of the study may compromises the internal validity of the study since difference at baseline between the levels of the provided care between pharmacies cannot be ruled out. It is likely that a part of the patients in the intervention groups will not be available for the intervention, because contact details are lacking or patients cannot be reached. Since in the control group these patients cannot be excluded this can cause a selection bias in the per-protocol analysis.

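### The secondary per-protocol analysis sets called intervention patients against all usual-care patients; the article admits the selection bias but neither corrects it nor limits how the result is read

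*Protocol article*

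**What the plan says.** In the protocol article, the Statistical analysis section states: "The primary analysis is based on the intention-to-treat (ITT) principle". It then adds a second analysis set: "In a per-protocol (PP) analysis we include in the intervention group only patients who actually received the call". Recruitment of patients names the comparator: "In a per-protocol (PP) analysis we will compare the patients who actually received counselling with patient who received usual care". Neither place restricts the usual-care side in a comparable way.

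The Limitations section expects incomplete delivery: "It is likely that a part of the patients in the intervention groups will not be available for the intervention". It draws the consequence itself: "Since in the control group these patients cannot be excluded this can cause a selection bias in the per-protocol analysis".

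Other sections describe how a patient comes to be called. Under Recruitment of patients, the pharmacist may leave out a patient whom the automated selection has picked. Under Exclusion criteria, eligible TelCIP-arm patients get an information letter, an invitation and a consent request; no counterpart is described for usual care. Under Intervention, the call falls 7 to 21 days after the first prescription, whereas the primary outcome counts from the date of that prescription. Under Other outcomes, calls and attempts are logged, with reasons for not calling.

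**The concern.** Being called is an event after allocation, and it depends on the pharmacist's decision, the patient's consent and whether the patient can be reached. Patients who fail at any of these steps leave the intervention side. Their equivalents stay on the usual-care side because nobody can identify them there. If the people who drop out would have been poorer adherers anyway, the called group looks better than usual care even when the call achieves nothing.

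At stake is the reading of the per-protocol result. The article does not call it descriptive, and its general rule of significance at p < 0.05 makes no exception for it. A difference there could be taken for the effect of the call when delivered, and the planned contrast does not estimate that.

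**Working it through.** **Inputs from the article (Sample size).** Adherence of 70% under usual care and 80% as the target; two-sided α of 0.05; power 0.80; ICC 0.02; 15 pharmacies with 30 patients per medication group, so 15 × 30 = 450 per class per arm.

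**The plan's own figure.** With pooled variance under the null and no continuity correction:

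n = [1.96 × √(2 × 0.75 × 0.25) + 0.8416 × √(0.70 × 0.30 + 0.80 × 0.20)]² / 0.10² = (1.2003 + 0.5119)² / 0.01 ≈ 293.2, rounded up to 294 per arm.

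This matches the article, so 10 points is the right yardstick.

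**Inputs the article does not give (assumptions).** The share called, r, and the adherence gap between called and uncalled patients. Both are varied below.

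**Bias when the call has no effect.** Let a and b be the adherence of patients who would and would not be called. Allocation leaves the same mixture in both arms.

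- Usual care: r·a + (1 − r)·b
- ITT difference: [r·a + (1 − r)·b] − [r·a + (1 − r)·b] = 0
- Per-protocol difference: a − [r·a + (1 − r)·b] = (1 − r)(a − b)

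Example: r = 0.60, a = 0.80, b = 0.55. Usual care is 0.60 × 0.80 + 0.40 × 0.55 = 0.48 + 0.22 = 0.70. ITT shows 70% v 70%; per-protocol shows 80% v 70%, which is 0.40 × 25 = 10 points.

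Spurious per-protocol difference, in percentage points:

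| Share called | Gap 10 | Gap 20 | Gap 25 |
|---|---|---|---|
| 50% | 5.0 | 10.0 | 12.5 |
| 60% | 4.0 | 8.0 | 10.0 |
| 70% | 3.0 | 6.0 | 7.5 |
| 80% | 2.0 | 4.0 | 5.0 |

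**Gap needed for a spurious 10 points**, from 10 / (1 − r): 20 points at 50% called, 25 at 60%, 33.3 at 70% and 50 at 80%. At 90% it would be 100 points, which is impossible with called patients at 80%.

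**Chance of a significant per-protocol result in one class with no effect** (normal approximation, ICC 0.02). The effective usual-care number is 450 / (1 + 29 × 0.02) = 450 / 1.58 = 284.8. The effective called number is 450r / [1 + (30r − 1) × 0.02]; at r = 0.70 this is 315 / 1.40 = 225.

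- 80% called, gap 10: about 7%
- 70% called, gap 10: about 11%
- 70% called, gap 20: about 32%
- 60% called, gap 25: about 70%

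All exceed the nominal 5%.

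**The alternative estimate.** Suppose the call adds δ in called patients and allocation works only through the call. Then the ITT difference is r·δ, and dividing by r returns δ; with no effect it returns 0. The per-protocol difference is δ + (1 − r)(a − b), so the selection term remains whatever the true effect.

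**The case against.** The strongest defence is that the bias is already disclosed and contained. The Limitations section describes this very mechanism, and Recruitment of patients gives possible selection bias as the reason for making ITT primary. The Discussion says the goal is the effect in daily practice, which ITT addresses. All of that stands. The main conclusion does not depend on the per-protocol contrast, and the absence of a complier-average analysis from a condensed article is not in itself a fault. What remains is that the article specifies, in two places, a contrast it calls prone to bias, and puts no limit on its use.

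A reader might infer more than the documents support:

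- **That the per-protocol analysis would manufacture the whole 10-point target.** This is arithmetically possible, but it needs low reach with a large gap, and the article gives neither figure.
- **That the bias must favour the intervention.** That is likely, since consenting and reachable patients are probably better adherers. But the article does not say which patients pharmacists leave out. If they pass over patients who are coping well, the bias shrinks or reverses.
- **That patients who never start are all lost from the called group.** Other outcomes records, for each call or attempt, whether the patient started. A non-starter identified during a call has received it and stays in.

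The alternative can also be challenged. The information letter and invitation in the TelCIP arms are a route to adherence other than the call, and this objection stands. Study design describes alternate assignment of pharmacies, which weakens allocation as an instrument; but any harm from that reaches the ITT comparison too, so it is no argument for the per-protocol contrast.

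**Conclusion.** The point holds as a fault in a secondary analysis. The per-protocol comparison is selected on one side only, and its expected value under no effect is (1 − share called) × (adherence gap), not zero. At 70–80% called with gaps of 10–20 points, that is about 2 to 6 points; 10 points is the result of a harsher scenario, not an expectation. These sizes rest on assumed reach and gap, on comparable mixtures of patients in the two arms, and, for the significance figures, on the article's ICC of 0.02. The direction is probably, but not certainly, in favour of the intervention. The primary ITT result is untouched. The remedy is cheap enough to be worth adopting.

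**What to change.** For the effect among those called, replace the per-protocol contrast with a complier-average effect. Within each medication class, divide the ITT difference in the proportion adherent (on the risk-difference scale) by the proportion of ITT intervention patients whom the online log shows as called. Give a confidence interval that allows for clustering by pharmacy. If the per-protocol contrast is kept, label it descriptive, report the share called and the reasons for not calling beside it, and draw no effect claim from it.

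The cost is one further analysis on data already collected; the per-protocol analysis needs the same link between call log and dispensing records. There are two downsides. The interval is wider than for ITT, by a factor of about 1/r if the share called is treated as fixed: 1 / 0.80 = 1.25 at 80% called and 1 / 0.60 = 1.67 at 60%. The estimate also assumes that allocation affects adherence only through the call. The information letter and invitation described for the TelCIP arms alone could breach this, so the plan should state the assumption and name that threat.

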### Handling and storage of data and documents

All patient data will provided to the Utrecht University by the participating pharmacies according to a procedure to protect the subjects’ privacy. Data with regard to the patients’ identity were coded anonymous by the participating pharmacies.

## Discussion

This is the first large intervention trial in The Netherlands to study the effect of telephone counselling by pharmacists on adherence. Although pharmacist can play an important role in improving adherence, in daily practice not all patients receive optimal care. The studied intervention is a way to deliver patient-centred care. And can be a solution to barriers in daily practice and that therefore more patients receive appropriate care. We also recognize that this intervention might not be appropriate for every individual patient, by including sufficient patients in 4 medication groups we expect to gain insight into which patients benefit most of this intervention.

The quality of the intervention depends on the competences and skills of the pharmacist. We try to assure treatment integrity by providing an interview protocol, an obligatory communication training and the obligation to document every counselling-call in an online database. Although it is likely that there will remain some differences between pharmacists, our goal is not to study the effect of an intervention in an ideal, perfectly controlled situation, but to study it in daily practice. We believe that this increases the external validity since it reflects current practice. The qualitative analysis of (a sample of) the telephone calls, will provide more insight in the intervention as provided by different pharmacists.

The intervention focusses on patient starting treatment and the aim of the intervention is to assess both practical and perceptual barriers that can influence adherent behaviour. These barriers can both be intentional or non-intentional and especially at the start of therapy it can be a mix of both. Moreover a recent study suggests that unintentional non-adherence is influenced by medication beliefs, chronic disease and socio-demographics [33]. So before a health care provider can tailor the intervention to intentional or non-intentional non-adherent behaviour, the barriers should first be assessed.

Assessment of adherence will be based on pharmacy data. Studies show that this is a valid method. In the Netherlands most prescriptions are filled for three months, irrespective of the frequency of dosing. Therefore, we expect to find enough contrast to assess the effect of the intervention on refill adherence.

We will conduct this study in different pharmacies in different regions of The Netherlands which will improve the external validity and will make it possible to perform an inter-pharmacy comparison.

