## Methods and design

### Study design

We will conduct a multicentre community pharmacy-based, cluster randomized controlled trial (CRT) (Figure 1). Pharmacies are alternately assigned to either group A or group B in a 1:1 ratio. Given the nature of the study design it is impossible for both the researchers and the pharmacists to be blinded to the group assignment. Each group consists of an intervention (TelCIP) arm and a usual care arm. The TelCIP arm in group A focuses on the same medication as the usual care arm in group B and vice versa.

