#### Inclusion criteria

• Receiving medication for a chronic condition for the first time in 12 months:

• Intervention arm A: starting with an antidepressant or bisphosphonate

• Intervention arm B: starting with a Renin-Angiotensin-System (RAS)-inhibitor or lipid-lowering drug.

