## Conclusion

Upon completion of this study will have knowledge if and for which group of high-risk patients, counselling by telephone at the start of a pharmacotherapy is (most) effective in improving adherence. Also will be clear how the intervention affects patients’ perceptions on medication and pharmaceutical care.

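### Comparing the call effect across the two medication pairs is also comparing group A with group B pharmacies, so claims about which medication group benefits should rest mainly on within-pair contrasts

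*Protocol article*

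**What the plan says.** The Study design section sets up a crossed allocation: "The TelCIP arm in group A focuses on the same medication as the usual care arm in group B and vice versa". The Inclusion criteria define the two pairs: "Intervention arm A: starting with an antidepressant or bisphosphonate" and "Intervention arm B: starting with a Renin-Angiotensin-System (RAS)-inhibitor or lipid-lowering drug".

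On assignment, the same Study design section states: "Pharmacies are alternately assigned to either group A or group B in a 1:1 ratio". The Abstract and the legend of Figure 1 describe the pharmacies as randomised.

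The Statistical analysis section plans a multilevel logistic model for the dichotomous outcome and, in a second analysis, this rule: "Effect modification is defined as a significant interaction (p < 0.10) between group allocation and the variable in question".

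The Discussion expects that "by including sufficient patients in 4 medication groups we expect to gain insight into which patients benefit most of this intervention". The Conclusion expects to learn "if and for which group of high-risk patients, counselling by telephone at the start of a pharmacotherapy is (most) effective". The Limitations section concedes that "difference at baseline between the levels of the provided care between pharmacies cannot be ruled out", but does not say what this means for comparisons between medication groups.

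**The concern.** Each pharmacy gives the call for one pair and usual care for the other, and which pair depends only on its group. Once the call effect may differ between pairs, the model has no freedom left to tell that difference from a difference in general adherence level between A and B pharmacies. The baseline difference that the Limitations section concedes thus acts very differently on different results. If it falls between the groups, it drops out of the balanced overall effect and enters doubled in the comparison of one pair with the other.

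The protocol presents the four medication groups as its route to learning who benefits most. Of the six possible drug-to-drug comparisons, four cross the pairs. In those four, an imbalance between A and B pharmacies could look like a call that works for one pair only, or could hide a real difference. They also carry much less information than 3,600 patients suggests, because part of their error depends on 15 pharmacies per group.

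The effect-modification rule adds an ambiguity. If group allocation there means call versus usual care, its interaction with pair is the A/B level difference. If it means A versus B, its interaction with pair is the call effect itself.

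**Working it through.** **Inputs from the protocol.** 30 pharmacies at 1:1, so 15 per group. ICC 0.02. 30 patients per medication group per pharmacy, so 60 per pair per pharmacy. Two-sided alpha 0.05 for the main effect, power 0.80, 70% versus 80% adherent, interactions tested at p < 0.10.

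**Assumptions.** Adherence rate 0.75 (the midpoint), so s² = 0.75 × 0.25 = 0.1875. Effects are additive on the analysis scale, and D is the same for all medicines. The share of the ICC common to all medicines in a pharmacy is not stated, so it is varied: all, half or none, the rest being specific to each medicine.

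**The plan's own figure.** The usual two-proportion formula with pooled variance gives 294 per arm, as stated. The design effect is 1 + 29 × 0.02 = 1.58, and 294 × 1.58 = 465, or 15.5 pharmacies of 30. The stated 15 × 30 = 450 gives power of about 0.79. The sizing of the main effect is not in question here.

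**The aliasing.** Let D be the level of A minus the level of B, and d1 and d2 the true call effects.
- Pair 1 (called in A): A1 − B1 = d1 + D
- Pair 2 (called in B): B2 − A2 = d2 − D
- Difference: (d1 − d2) + 2D
- Equally weighted average: (d1 + d2)/2, free of D

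With group, pair and call coded ±1, call × pair equals group in all four cells (five columns, rank 4). With four drug-specific effects plus a group term the rank is 8 of 9. The unidentified direction raises both effects in one pair and lowers both in the other, so the contrasts antidepressant versus bisphosphonate and RAS-inhibitor versus lipid-lowering drug are unaffected.

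Illustration: with a true effect of 10 points in both pairs, an assumed D of 2 points shows 12 and 8, and D of 5 points shows 15 and 5. The average is 10 each time.

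**Precision when D is chance only.** With the ICC fully shared:
- Var(D) = 2 × 0.02 × 0.1875/15 = 0.0005, so SD(D) = 2.2 points and SD(2D) = 4.5 points
- Patient-level part = 4 × 0.98 × 0.1875/900 = 0.000817
- Var(between-pair difference) = 4 × 0.0005 + 0.000817 = 0.002817, SE 5.3 points, 71% of the variance from D
- Pooled effect: √(0.000817/4) = 1.4 points

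A medicine-specific ICC part u adds 4u × 0.1875/30 to the between-pair variance. The pooled variance is a quarter of the between-pair variance without the D term. The within-pair variance is 4 × 0.98 × 0.1875/450 + 4u × 0.1875/15. The 80%-power difference at p < 0.10 is (1.645 + 0.842) × SE.

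| ICC shared | Between-pair SE | Detectable | Pooled SE | Within-pair SE | Detectable |
|---|---|---|---|---|---|
| all (u = 0) | 5.3 | 13.2 | 1.4 | 4.0 | 10.0 |
| half (u = 0.01) | 4.5 | 11.3 | 1.6 | 4.6 | 11.5 |
| none (u = 0.02) | 3.6 | 9.0 | 1.8 | 5.1 | 12.8 |

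All entries are in percentage points. A simulation of 20,000 trials with no true effect and a fully shared ICC gave an SD of 5.3 for the between-pair difference and 1.4 for the pooled effect.

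**If D also had a systematic part (size assumed).** The chance of p < 0.10 with no true difference is P(|Z + 2D/SE| > 1.645), against a nominal 10%:

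| Assumed D | ICC all shared | half shared | none shared |
|---|---|---|---|
| 2 points | 19% | 23% | 30% |
| 3 points | 31% | 37% | 50% |
| 4 points | 45% | 55% | 71% |

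A correct multilevel standard error does not prevent this, because it carries only the chance part of D.

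**The case against.** Every two-group cluster trial estimates effect plus group difference. Randomisation makes the group difference zero on average, and the pharmacy random effect carries its chance part into the standard error. This stands: if pharmacies are truly randomised, the cross-pair contrast is unbiased and merely imprecise. A reader might infer that it is invalid, or that no statement about medication groups is supported. The documents do not bear that out, since the pooled effect, the two within-pair drug contrasts and patient-level modifiers studied inside a pair are all free of D under the stated assumptions.

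A systematic gap is not shown either. The Limitations section speaks of differences between pharmacies, not between groups A and B. The only route in the text is the alternate assignment in Study design, set against the randomisation described elsewhere. That makes a systematic gap possible and says nothing about its size.

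The protocol names no between-pair interaction as an analysis, it powers only the main effect, and a list of contrasts may be left to an analysis plan. This is also fair, and low interaction power contradicts no stated power claim. But the Discussion ties insight into who benefits to the four medication groups without a limit, and most comparisons among those four cross the pairs.

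Finally, a fixed group term cannot separate D, but a pharmacy-level covariate such as pre-trial adherence from the dispensing records could absorb the measured part. That is right, and it is a useful addition rather than an answer to the aliasing.

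**Conclusion.** The point holds for comparisons across the two medication pairs and no further. There, a common A/B level gap D appears as 2D. In the equally weighted pooled effect it cancels, and within a pair it does not enter.

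Under true randomisation the consequence is imprecision: a standard error of 5.3, 4.5 or 3.6 points according to how much of the ICC is shared. The detectable differences of about 13, 11 or 9 points compare with the 10 points for which the main effect is sized. With nothing shared, the between-pair contrast does meet that mark. Under alternate assignment a systematic gap is possible. An assumed D of 2 to 4 points would then raise false positives from 10% to about 19–45% with the ICC fully shared, and to about 23–55% with half shared.

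These figures rest on the rate of 0.75, planned recruitment in every pharmacy, and a D that is equal across medicines and additive on the analysis scale. For the planned logistic model the algebra holds if D is constant in log-odds, and the percentage-point figures are then approximate.

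This does not threaten the trial's overall result. It limits what may be concluded about which medication group benefits most, and the remedy is cheap.

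**What to change.** In Statistical analysis:
1. State that group allocation in the effect-modification rule means call versus usual care.
2. Base medication-group effect modification on antidepressant versus bisphosphonate and on RAS-inhibitor versus lipid-lowering drug.
3. Report any cross-pair difference as exploratory, with a pharmacy-level standard error and the statement that it assumes equal levels in A and B pharmacies. Adjustment for pre-trial adherence per pharmacy from dispensing records could reduce the measured part of the gap.
4. Estimate the pooled effect with the two pairs equally weighted, or with medication class and A/B group as fixed terms, so that D cancels even if recruitment is uneven.

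In the Discussion and Conclusion, rest claims about which medication group benefits on the pooled effect and the within-pair contrasts. Reconcile the alternate and random descriptions of assignment.

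The cost is some analysis work, some wording and a weaker claim about differences across the pairs. The within-pair contrasts are protected from D but are not highly powered: they detect about 10 to 13 points, so they too should be reported with their intervals.
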